### Outcomes

The primary outcome is a composite endpoint including the occurrence of intraoperative and postoperative complications within 6 weeks of surgery. Intraoperative complications will be defined as injury to surrounding organs (bladder, ureters, rectum, colon, small intestine) or bleeding requiring immediate resumption, intraoperative transfusion and/or decreasing the patient’s haemoglobin by more than 2 points compared to the last known pre-operative blood test. Postoperative complications will be defined according to the Clavien-Dindo classification.

Regarding secondary outcomes, the need for conversion during surgery will be collected.

Post-operative pain at day 0 will be evaluated by the maximum daily pain felt on arrival in ambulatory surgery and at hour 3 after return from the block. Short-term postoperative pain during the first week after surgery will be measured by a numerical scale (0 to 10), determined on a daily telephone call. The consumption of analgesics other than those planned in the study in the immediate postoperative period and within 7 days will also be recorded. The duration of postoperative reflex ileus will be measured between the day of the operation and the resumption of a transit (appearance of the first gas) in hours. The duration of the operation from the incision to the end of the closure (in minutes). The duration of hospitalisation will be evaluated in days and the possibility of returning home by the time in hours between the surgical incision and the achievement of a Chung≥ score of 9/10. Sexual disorders: sexual life will be assessed by the difference in the specific validated score (self-questionnaire) (PISQ12 with a score ranging from 0 to 48) between the inclusion date and 3 months after surgery for sexually active women. The visual comfort, satisfaction and feeling of safety of the surgeon and the operating assistant will be evaluated via a Likert scale.

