### Sample size calculation

Based on the figures found in two studies on large uteri (Daraï et al., 2001; Hwang et al., 2002) and Baekelandt’s study of hysterectomies (Baekelandt et al., 2019), for an alpha risk of 5% and a power of 90%, a superiority study with an expected complication rate of 37% with laparoscopy and 15% with the vaginal route (i.e. an RR of 0.5 and therefore a relative reduction in risk of 50%) will need to include 119 patients per group, i.e. 236 in total. In order to compensate for possible loss of sight, 248 patients will be included.

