### Study design

An information brochure on the study will be given to all patients who meet the inclusion criteria of the study at the preoperative consultation. An evaluation of pain by EVA scale will be carried out during this consultation.

After obtaining the patient’s consent on the day of the operation, the allocation between the two groups will be done by randomisation. This randomisation will be stratified on the centre and uterine volume (280-500g; > 500g). The randomisation list will be a randomised computer list established before the beginning of the study. It will be balanced by blocks of variable size and centralised via the Ennov Clinical web platform.

Two groups of patients will be constituted: a “laparoscopic approach” group and a “vNOTES” group. Patients will not know their group of assignment.

All hysterectomies will be performed by vNOTES-trained surgeons (20 procedures performed) who will follow the standard operating procedure. In women assigned to the experimental arm, the surgeon will perform a hysterectomy with the vNOTES medical device. In the women assigned to the control arm, the surgeon will perform a laparoscopic hysterectomy.

A questionnaire assessing visual comfort, feeling of safety and satisfaction on Lickert scales will be completed immediately after surgery by the operator and the operating assistant.

The care provided by the anesthetists and nurses will be standardised and similar in both groups. To limit bias, in all cases the patient will have abdominal dressings as if it underwent a laparoscopy.

Once returned to the ward, all participants will be assessed every 2 hours and discharged home when the patient’s condition allows(Chung score ≥ 9/10).

Telephone interviews by the department CRA, blinded to the allocation group will be conducted daily for the first week to assess postoperative pain.

A follow-up visit by an independent adjudication committee, blinded to the allocated group will be performed 6 weeks postoperatively or earlier if a complication brings a patient to consult.

Finally, a telephone call will be made at 3 months to evaluate the sexual impact by a questionnaire (PISQ12 with a score ranging from 0 to 48) (Table I).

**Table I t001:** Conduct of the study.

Visits	V1	V2	V3	V4	V5	V6
Title of the visit	Pre-operative selection visit	Day of the intervention	Immediate post-operative follow-up	Telephone follow-up D1-D7	Post-operative visit at 6 weeks	Questionnaire at 3 months
Information	X					

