### Statistical analysis

The included population will described globally and by group (vNOTES vs laparoscopic approach). The main analysis will be performed according to the intention-to-treat principle. The frequency of patients presenting with at least one complication will be estimated in each group, as well as the 95% confidence interval of this frequency. The effect of the surgical strategy will be estimated by the relative risk and the 95% confidence interval. The resulting p-value of Fisher’s exact test will also be given. As the secondary objectives are exploratory, no statistical test will be performed (i.e. no p-value will be estimated), according to the new NEJM recommendations.

For the qualitative secondary endpoints, the relative risk and its confidence interval will be given. For quantitative endpoints, differences in means will be calculated, as well as their 95% confidence intervals.

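### The PISQ-12 comparison is planned as an unadjusted difference in mean change; adding the inclusion score as a covariate would give a somewhat narrower confidence interval (minor, exploratory outcome)

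*Protocol article*

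**What the plan says.** Three places in the protocol article bear on this point.

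- **Outcomes.** For the secondary outcome on sexual function, "sexual life will be assessed by the difference in the specific validated score (self-questionnaire"), the instrument being PISQ-12 on a 0 to 48 scale. The difference is taken "between the inclusion date and 3 months after surgery for sexually active women". The outcome is therefore a within-woman change that needs a score at inclusion.
- **Statistical analysis.** One sentence covers all quantitative secondary endpoints: "For quantitative endpoints, differences in means will be calculated, as well as their 95% confidence intervals". No baseline covariate is mentioned. The same section sets their status: "As the secondary objectives are exploratory, no statistical test will be performed".
- **Study design and Table I.** The questionnaire is described only at the last contact: "Finally, a telephone call will be made at 3 months to evaluate the sexual impact by a questionnaire". Table I marks it at V6 and at no earlier visit. The Data collection section lists PISQ-12 but gives no time for it.

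Taken as written, the planned comparison is the mean change in one arm minus the mean change in the other, with a 95% interval.

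**The concern.** A change score subtracts the inclusion score with a coefficient of exactly 1, whatever the real correlation between the two measurements. Unless the best coefficient happens to be 1, the subtraction carries more baseline variation into the comparison than it removes, or than it needs to. Regression on the inclusion score lets the data set the coefficient.

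Precision is at stake, not validity. No p-value is planned for secondary outcomes, so the estimate and its interval are all that will be reported on sexual function. The analysis is limited to sexually active women, so it uses fewer than all the randomised women ("248 patients will be included"). By how many is not stated. The trial was sized on complications, not on this outcome.

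**Working it through.** **Inputs.** The article gives no SD, correlation, expected effect or precision for PISQ-12, so there is no figure of the plan's own to reproduce. From the article: the outcome is a change from inclusion to 3 months, the estimator is a difference in means with a 95% interval, and at most 248 women contribute (about 124 per arm). Assumed: the correlation rho between the inclusion and 3-month scores, over a range, and, for the main result, the same SD s at both times.

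**Step 1: variance per woman.**

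- Change score: 2(1 − rho)s²
- 3-month score adjusted for the inclusion score: (1 − rho²)s²
- Ratio, adjusted to change: (1 − rho²) / [2(1 − rho)] = (1 + rho)/2, which is below 1 for every rho below 1
- Ratio of standard errors: sqrt((1 + rho)/2)

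**Step 2: numbers.** The half-widths are in units of s, with 124 per arm as the upper bound: 1.96 × sqrt(2 × variance/124).

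| Assumed rho | Variance ratio | SE ratio | Interval narrower by | Half-width, change | Half-width, adjusted |
|---|---|---|---|---|---|
| 0.3 | 0.65 | 0.806 | 19% | 0.295 | 0.237 |
| 0.5 | 0.75 | 0.866 | 13% | 0.249 | 0.216 |
| 0.7 | 0.85 | 0.922 | 8% | 0.193 | 0.178 |
| 0.8 | 0.90 | 0.949 | 5% | 0.157 | 0.149 |
| 0.9 | 0.95 | 0.975 | 2.5% | 0.111 | 0.109 |

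With fewer evaluable women both half-widths grow, but their ratio stays the same.

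**Step 3: simulation.** With 3,000 replicates, the SE ratios at 60 and 124 women per arm were 0.805 and 0.813 (rho 0.3), 0.875 and 0.873 (rho 0.5), and 0.926 and 0.923 (rho 0.7). These agree with the formula.

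**Step 4: unequal SDs.** Let the SD be s0 at inclusion and s1 at 3 months. The change variance is s0² + s1² − 2·rho·s0·s1 and the adjusted variance is s1²(1 − rho²). The first minus the second is (s0 − rho·s1)², which is never negative. In large samples adjustment therefore never loses precision, though the percentages in the table would differ.

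**Step 5: does the outcome have to be redefined?** Write the regression on the change as Y − B = a + bT + cB, where Y is the 3-month score, B the inclusion score and T the arm. Moving B across gives Y = a + bT + (c + 1)B. The arm coefficient b is the same. In the simulation the two estimates differed by less than 1e-14. The loss comes from leaving out the covariate, not from defining the outcome as a change.

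**Step 6: chance imbalance.** Given an observed inclusion-score difference d between arms, the unadjusted change estimate is displaced by (rho − 1)d. As an illustration with an assumed 60 evaluable women per arm, the SE of d is sqrt(2/60) = 0.18 SD. At rho 0.5, an imbalance of that size displaces the estimate by 0.5 × 0.18 = 0.09 SD. Over repeated randomisation this averages to zero, and the unadjusted interval already allows for it.

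**The case against.** The strongest reply is that nothing here is wrong. Under randomisation, a difference in mean change is unbiased and its interval has valid coverage. That stands. A reader might infer from talk of regression to the mean that the planned estimate is biased. The documents do not support this: the displacement in step 6 is conditional on a chance imbalance and is part of the sampling variation that the interval reflects.

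A second reply is that the sentence in the Statistical analysis section is generic, that an adjusted mean difference is still a difference in means, and that covariates may be set in an analysis plan that is not shown. This carries some weight, because the article does not expressly exclude adjustment. But it states both the outcome and the estimator, and read plainly the estimator is unadjusted. Saying otherwise needs a sentence.

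A third reply is that the gain is small and rests on an assumed correlation. This also stands. A reader might take the gain at rho 0.5, equivalent to one third more evaluable women (1/0.75 = 1.33), as the general result. It applies only at that value; at rho 0.9 the equivalent is about 5% more (1/0.95 = 1.05).

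A reader might also infer that the outcome must be changed to the 3-month score. Step 5 shows that this is unnecessary.

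Finally, the schedule shows no inclusion questionnaire, so as it stands neither the change nor the adjusted analysis could be computed. That inconsistency is more serious than the choice of estimator and has to be settled first. It does not remove the point: once the inclusion score is collected, as the outcome definition requires, using it only by subtraction gives up some precision.

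**Conclusion.** The point holds as a minor one. As written, the plan compares PISQ-12 by an unadjusted difference in mean change. This is valid but less precise than an estimate adjusted for the inclusion score. Under equal SDs, the 95% interval would be about 19% narrower at rho 0.3 and 2.5% narrower at rho 0.9. The documents give no value of rho, no SD and no number of sexually active women, so the gain cannot be placed within that range. The outcome is exploratory and untested, and no sample size or error rate depends on the width of its interval.

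**What to change.** 1. Reconcile Table I and the Study design section with the Outcomes section, so that the PISQ-12 score at inclusion is shown as collected.
2. Leave the outcome definition as it is. Add one sentence to the Statistical analysis section: the PISQ-12 difference between arms will be estimated by linear regression with the inclusion PISQ-12 score as a covariate (and the randomisation strata of centre and uterine volume, if wished), and reported as an adjusted mean difference with its 95% confidence interval. Either the change or the 3-month score may be the response. The unadjusted mean change per arm can be shown descriptively.

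The cost of the second step is wording only, provided that the inclusion score is collected. If it is not collected at present, the first step adds one questionnaire per woman at inclusion, which the existing outcome definition already requires.

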Eligibility Criteria	X					
History of comorbidities	X					
Consent		X				
Randomisation		X				
Intervention*		X				
Adverse events		X	X	X	X	
Chung's score **			X			
Post-operative pain assessment ***			X	X		
Clinical examination ****					X	
Sexuality Questionnaire						X

X specific acts to research; *According to the allocated group; **Chung score; ***by scale from 0 (no pain) to 10 (maximum pain); ****standardised clinical examination: general condition, BP, abdominal palpation, vaginal examination.

The study protocol has been validated (N° clinical trial : NCT05884658).

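### The sexual-function outcome is a change in PISQ-12 from inclusion, but the printed schedule times PISQ-12 only at 3 months

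*Protocol article*

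**What the plan says.** The Outcomes section of the protocol article states that "sexual life will be assessed by the difference in the specific validated score (self-questionnaire) (PISQ12 with a score ranging from 0 to 48"), taken "between the inclusion date and 3 months after surgery for sexually active women". So the outcome is a within-woman change, restricted to a subset.

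The Study design section mentions the instrument once: "Finally, a telephone call will be made at 3 months to evaluate the sexual impact by a questionnaire", which it names as PISQ-12. In Table I the row "Sexuality Questionnaire" carries a single X in the last column, V6, which is titled "Questionnaire at 3 months". V1 (selection visit) and V2 (day of the operation) are empty in that row. The Data collection section includes PISQ-12 among the data gathered but does not say when.

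On analysis, the Statistical analysis section says: "For quantitative endpoints, differences in means will be calculated", with 95% confidence intervals. It treats the secondary objectives as exploratory and reports no p-values for them.

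Pre-operative pain is handled differently. The Study design section says "An evaluation of pain by EVA scale will be carried out during this consultation", that is, the preoperative consultation, although Table I has no matching entry.

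**The concern.** A change score needs a measurement at each end. The article defines the outcome by both ends and then schedules only the later one. A site working from Table I would have no prompt to give the questionnaire before surgery, and a pre-operative score cannot be obtained afterwards except by recall. Consent, randomisation and surgery all fall on the same day (V2), so the time between inclusion and surgery is short and a step that is not on the schedule is easily missed.

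The restriction to sexually active women raises a second gap. The article does not say when that status is judged, and no pre-operative item on sexual activity is listed. The Abstract also names the return to sexual life as a secondary outcome, and this too is hard to interpret without knowing the status before surgery.

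At stake is whether one declared secondary outcome can be reported as defined, in a population fixed before treatment.

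**Working it through.** The plan gives no figure to reproduce here. The check sets the sections side by side.

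**Scores needed and scores scheduled**

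- Outcomes section: PISQ-12 at inclusion and at 3 months. Needed: 2.
- Study design text: PISQ-12 at the 3-month telephone call. Scheduled: 1.
- Table I: one X, at V6. Scheduled: 1, the same one.
- Data collection section: PISQ-12 named with no time. It neither supplies nor rules out a baseline, and the 3-month call alone would satisfy it.

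Needed minus scheduled = 2 − 1 = 1, and the missing score is the one at inclusion.

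**Is the X in the right column?** Table text read from a PDF can shift, so the other rows were compared with the narrative. Consent and randomisation fall under V2, the day of the operation, as the text says. The clinical examination falls under V5, the 6-week visit, as the text says. The columns are aligned, and the text describing the 3-month call independently places the questionnaire at V6.

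**What can be estimated under the printed schedule**

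- Change, Y(3 months) − Y(inclusion): undefined for a woman with no inclusion score.
- Level, Y(3 months): available. The difference in mean level between randomised groups can be computed, but it is not the outcome as defined, and the subset of sexually active women would still need a rule.

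**Optional: what a baseline would add to precision**

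Let ρ be the correlation between the baseline and follow-up scores, with equal variances at both times. The article gives no ρ, so the values below are assumptions. The variance of the estimated group difference, relative to comparing follow-up scores alone (= 1), is:

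- change score: 2(1 − ρ)
- follow-up adjusted for baseline: 1 − ρ²

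Results:

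- ρ = 0.1: change 2 × 0.9 = 1.8; adjusted 1 − 0.01 = 0.99
- ρ = 0.3: change 2 × 0.7 = 1.4; adjusted 1 − 0.09 = 0.91
- ρ = 0.5: change 2 × 0.5 = 1.0; adjusted 1 − 0.25 = 0.75
- ρ = 0.7: change 2 × 0.3 = 0.6; adjusted 1 − 0.49 = 0.51

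Adjustment therefore lowers the variance by 1% to 49% over this range. A change score is less precise than the follow-up score alone when ρ is below 0.5. These are general formulas. They show what a baseline could be used for and are not evidence of an error in this plan.

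**The case against.** The strongest reply is that Table I is not a complete list. It leaves out the pre-operative pain score and the questionnaire for the operator and assistant, both of which the text says are collected. Absence from the table does not prove that a measurement is not taken. The outcome definition itself implies an inclusion score, and the full protocol may schedule one. This stands in part: a reader might infer that no baseline form exists or that every change score will be missing, and the article does not establish that. But the two cases differ. The pain score is missing from the table yet stated in the narrative, whereas a baseline PISQ-12 is missing from both. The inconsistency is between printed statements, so it is not just detail lost in condensing a protocol.

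A second reply is that the outcome would not be lost. This is right: randomisation makes a comparison of 3-month scores valid, and the outcome is exploratory.

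A third concerns selection. A reader might infer that the subset will be chosen by sexual activity at 3 months, which would condition on something the operation could influence. The article does not say so. It leaves the timing open, and the bias would arise only under that choice.

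A fourth concerns pain. It is tempting to call it an error that pre-operative pain is collected but does not enter the analysis of post-operative pain. The documents do not support this. An unadjusted difference in means between randomised groups is valid, baseline pain may serve for description, and adjustment is commonly left to an analysis plan, which is not shown here.

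**Conclusion.** The point holds as an internal inconsistency. The outcome definition requires PISQ-12 at inclusion and at 3 months, while the design text and the visit table provide only the latter. Followed as printed, the schedule leaves the change score without a baseline for all women and pre-operative sexual activity unrecorded; the 3-month comparison between groups remains possible.

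The consequence is confined to one secondary, exploratory outcome, and the primary complication analysis is untouched. It is worth correcting before enrolment because the missing measurement cannot be taken later. The conclusion rests on the article alone. If the full protocol already schedules a pre-operative PISQ-12, what remains is a correction to Table I and the Study design text.

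**What to change.** - Add PISQ-12 and a sexual-activity item to Table I at V2, to be completed after consent and before randomisation, and say so in the Study design text. V1 is less suitable because Table I places consent at V2, so a research questionnaire at V1 would precede consent. Asking only that it be done before surgery would not ensure completion before allocation.
- State in the Outcomes section that the analysed women are those sexually active at that V2 assessment.
- If a pre-operative form is not wanted, redefine the outcome as the 3-month PISQ-12 score and state how the analysed women are identified.

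The cost is one 12-item form and one status question per woman before surgery, plus a change to one row of Table I and a few words of text.

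Optional, for precision only: enter the pre-operative pain score in Table I at the consultation where the text already places it, and estimate the mean differences in 3-month PISQ-12 and in post-operative pain with adjustment for the baseline value. For pain this needs no new data. The gain is ρ² of the variance, with ρ unknown.

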### Data collection

Demographic data including age, weight (kilograms), height (cm), BMI (Kg/m2), medical, surgical and obstetric history will be collected directly in the observation notebooks as the study visits take place.

Also collected will be the uterine volume, estimated by pelvic ultrasound or by pelvic MRI if available, the benign uterine pathology requiring the intervention (fibroid, adenomyosis, endometrial hyperplasia, bleeding), the general condition of the patient, the solidity of the vaginal suture, postoperative pain and use of analgesics, the possible occurrence of the above-mentioned complications and sexual disorders with the PISQ 12 scale. These data will be validated by the investigator who will sign the observation notebooks. Missing data will be justified.

### Statistical analysis

The included population will described globally and by group (vNOTES vs laparoscopic approach). The main analysis will be performed according to the intention-to-treat principle. The frequency of patients presenting with at least one complication will be estimated in each group, as well as the 95% confidence interval of this frequency. The effect of the surgical strategy will be estimated by the relative risk and the 95% confidence interval. The resulting p-value of Fisher’s exact test will also be given. As the secondary objectives are exploratory, no statistical test will be performed (i.e. no p-value will be estimated), according to the new NEJM recommendations.

For the qualitative secondary endpoints, the relative risk and its confidence interval will be given. For quantitative endpoints, differences in means will be calculated, as well as their 95% confidence intervals.

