**Materials and Methods:**

A randomised, double-blind, superiority trial will be performed at five hospital centres. Women with benign uterine pathology requiring hysterectomy and with a large uterus (> 280g) will be randomised to receive either laparoscopic or vNOTES hysterectomy.

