## Material and Methods

### Type of study

This is a prospective, open-label, multicentre, randomised, parallel-group superiority study stratified on centre and uterine volume (280-500g; >500g). It evaluates conversion and intraoperative and postoperative complications within 6 weeks of surgery using the transluminal natural orifice vaginal endoscopic system for hysterectomies (vNOTES) versus laparoscopic hysterectomy.

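### Randomisation is stratified, but the only primary test named is an unstratified Fisher's exact test, which costs 2 to 3 points of power at RR 0.5 and leaves the deciding criterion open

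*Protocol article*

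**What the plan says.** The design is stratified, and the article says so twice. Under Type of study it is a "parallel-group superiority study stratified on centre and uterine volume (280-500g; >500g"), and under Study design "This randomisation will be stratified on the centre and uterine volume (280-500g; > 500g"). With five centres and two volume classes there are up to 5 × 2 = 10 strata.

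The primary outcome is binary. Under Statistical analysis, "The frequency of patients presenting with at least one complication will be estimated in each group", with a 95% confidence interval, by intention to treat. Then: "The effect of the surgical strategy will be estimated by the relative risk and the 95% confidence interval", and "The resulting p-value of Fisher’s exact test will also be given". The section mentions no stratification factor, names no method for the interval, and does not say whether the interval or the p-value settles superiority.

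The Sample size calculation uses a 5% alpha risk and 90% power. It assumes an "expected complication rate of 37% with laparoscopy and 15% with the vaginal route", but describes this as an RR of 0.5, and arrives at 119 per group, 236 in total, raised to 248 for losses.

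**The concern.** After stratified randomisation, an analysis that ignores the strata tends to overstate the variance of the treatment effect if the strata predict outcome. Fisher's exact test is also conservative on a two-group table of this size. Both errors work against finding a real difference. Separately, a relative-risk interval and a Fisher p-value come from different procedures, so one can indicate a difference while the other does not. At stake are a few points of power, some precision, and a possible split result on the primary outcome with no rule to resolve it.

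**Working it through.** **Inputs from the article.** Alpha 5% (taken as two-sided; sidedness is not stated), power 90%, control risk 37%, RR 0.5 (so 18.5%) or 15%, 119 per group, 248 in total (124 per group if 1:1).

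**Assumed.** Log-Wald interval for the relative risk; stratum sizes and risks in the simulations. The article gives none of these.

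**Step 1: the plan's own sample size.** Unpooled formula: n = (1.960 + 1.282)² × [p₁(1−p₁) + p₂(1−p₂)] / (p₁−p₂)².

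- 37% vs 18.5%: 10.507 × (0.2331 + 0.1508) / 0.0342 = 117.9, so 118 per group and 236 in total. The pooled formula gives 122 and the arcsine formula 120.
- 37% vs 15%: 78.3 unpooled, 82 pooled. Here RR = 15/37 = 0.41.

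The stated size therefore matches RR 0.5 with a normal-approximation test, not the 15% rate and not Fisher's test.

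**Step 2: exact size and power.** All possible two-group tables were enumerated and weighted by their binomial probabilities, two-sided 5%:

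| Per group | True risks | Fisher | Chi-square, uncorrected | Log-Wald RR interval | Interval excludes 1, Fisher p > 0.05 |
|---|---|---|---|---|---|
| 119 | 27.75% both | 3.6% | 5.1% | 4.8% | 1.2% |
| 119 | 37% vs 18.5% | 87.1% | 89.9% | 89.4% | 2.4% |
| 124 | 27.75% both | 3.6% | 5.0% | 4.7% | 1.2% |
| 124 | 37% vs 18.5% | 88.4% | 90.9% | 90.5% | 2.1% |
| 124 | 37% vs 25% | 48.1% | 53.4% | 52.8% | 4.7% |
| 124 | 37% vs 15% | 97.3% | 98.2% | 98.0% | 0.7% |

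At RR 0.5, Fisher's test loses 89.9 − 87.1 = 2.8 points with 119 per group and 90.9 − 88.4 = 2.5 points with 124. The opposite disagreement (Fisher significant, interval including 1) had probability 0.0% in every scenario tried.

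**Step 3: an example of disagreement.** Take 46/124 complications with laparoscopy and 31/124 with vNOTES. RR = 31/46 = 0.674. SE of log RR = √(1/31 − 1/124 + 1/46 − 1/124) = 0.195. The interval is exp(−0.395 ± 1.96 × 0.195) = 0.46 to 0.99, which excludes 1. Fisher's p = 0.054.

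**Step 4: how much the strata matter.** Two simulations of 248 patients in 10 strata compared Fisher's test, the uncorrected chi-square and the Cochran-Mantel-Haenszel (CMH) test. The gap between chi-square and CMH is the part due to stratification.

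| Simulation | True effect | Assumed stratum risks | Fisher | Chi-square | CMH | CMH − chi-square |
|---|---|---|---|---|---|---|
| A (8,000 runs) | RR 0.5 | equal | 88.7% | 90.5% | 90.5% | 0.0 |
| A | RR 0.5 | volume log-OR 0.7 | 89.5% | 91.1% | 91.4% | 0.3 |
| A | RR 0.5 | volume log-OR 1.0 plus centre effects | 90.1% | 91.7% | 92.2% | 0.5 |
| B (20,000 runs) | RR 0.5 | 0.22 to 0.50 | 88.6% | 91.2% | 91.5% | 0.3 |
| B | RR 0.5 | 0.13 to 0.65 | 89.2% | 91.6% | 92.6% | 0.9 |
| B | RR 0.6 | 0.24 to 0.52 | 68.4% | 73.1% | 74.2% | 1.1 |
| B | RR 0.6 | 0.14 to 0.66 | 68.8% | 73.9% | 77.5% | 3.5 |

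Differences in the last column were taken before rounding where more decimals were available. The Monte Carlo standard error of each power figure is about 0.3 points in A. Under no treatment effect in B, CMH had size 4.7% to 4.9% and Fisher 3.6% with equal strata, falling to 2.7% with the widest spread.

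**The case against.** Several stronger readings are tempting, and the article does not support them.

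- **Ignoring the strata is the main loss.** A reader who compares Fisher directly with CMH might infer this. That comparison makes two changes at once. At RR 0.5 most of the gain comes from replacing Fisher's test; stratification adds about 0 to 0.6 points, or 0.9 with the widest assumed spread of risks. Larger gains need both a weaker effect and strongly prognostic strata.
- **The strata are known to predict complications.** The Introduction and Discussion say large uteri carry more complications. Nothing says that volumes above 500g differ from 280-500g, or that centre matters.
- **The relative risk is fixed as unadjusted.** That is an inference. Estimator and interval method are often left to an analysis plan, which is not shown here and could stratify. What the article does fix by name is Fisher's test.
- **The trial is underpowered.** At its stated 37% vs 15%, Fisher's test has about 97% power. The shortfall applies at RR 0.5, the effect the stated sample size reproduces.
- **The analysis is invalid.** It is not. Fisher's test keeps its size below 5%, and a disagreement needs a borderline result.

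These limits reduce the size of the point. What stands is that the named test is unstratified and conservative, falls short of 90% power at RR 0.5 even with all 248 patients analysed, and sits beside an interval with no stated order of precedence.

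**Conclusion.** The point holds as a moderate one, worth correcting before data are seen. Fisher's actual size is about 3.6% at a common risk near 28%. Its power at RR 0.5 is about 87% to 88% rather than 90%, a loss of 2 to 3 points that comes mostly from the test itself. Disregarding the strata costs little at RR 0.5 and somewhat more at weaker effects if the strata are strongly prognostic. A relative-risk interval that excludes 1 beside a non-significant Fisher p-value would occur in about 2% of trials at RR 0.5 and about 5% at 37% vs 25%, and nothing says which prevails. The error is in the conservative direction.

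The size and power figures assume a two-sided 5% level and 1:1 allocation; the disagreement figures also assume a log-Wald interval. The stratification figures rest on assumed stratum sizes and risks.

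**What to change.** Make the primary analysis the Mantel-Haenszel relative risk stratified on the randomisation factors, with its 95% confidence interval, and take the p-value from the matching CMH test without continuity correction. Name one of the two as the criterion for superiority. This is still needed because they are not identical: in simulation B at RR 0.5, CMH rejected about 0.4 to 0.5 points more often than the Mantel-Haenszel interval. State in advance how sparse centre strata are handled, for example by pooling small centres within volume class. Keep the unstratified relative risk with Fisher's test as a sensitivity analysis. Stratifying the secondary outcomes, which are exploratory and untested, is optional.

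The cost is a short amendment, with no extra patients or data, since both factors are needed to randomise. The small downside is that the conservatism of the exact test is given up and sparse strata need a rule.
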